### Randomisation

The participants will be randomised to either the PREVSAM model or to treatment as usual (TAU). Sequentially numbered, opaque, sealed envelopes containing notes marked ‘PREVSAM’ or ‘TAU’ are block-randomised by a computer programme in blocks of six (three of each), in order to ensure an even distribution. These are placed in a box at each participating centre. The allocation sequence will not be accessible to the persons who enrol participants and assign intervention. Enrolment and assignment of intervention will most often be done by a person from the interdisciplinary team.

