##### Patient-reported risk for sickness absence

The ÖMPSQ-SF will be used primarily as a screening instrument for the planned study [26], but also as an outcome measure for *changed risk* (proportion lowering their risk by scoring < 40 p at follow-up). The original Örebro Musculoskeletal Pain Screening Questionnaire (ÖMPSQ) was developed as a screening questionnaire for identifying patients at risk of developing persistent back pain problems, and has been shown to have acceptable reliability and validity [43]. It is often described as predictive for persistent pain, but studies have usually evaluated the predictive validity of the questionnaire for sickness absence [26, 43]. The ÖMPSQ-SF is self-administered and includes item 7, 9, 13–16, 19–21 and 25 from the original ÖMPSQ. The item contains a statement or an assertion which the respondents rate on 11-point Likert scales from 0, referring to absence of impairment, to 10, severe impairment. A cut-off of 50 points has been recommended to identify those of higher risk of future disability and sickness absence [26]. However, clinical experience as well as recent studies have shown that a cut off of 40 points might be better to use [29]. Although the instrument was primarily developed for people with back pain, the questions regarding musculoskeletal pain are general and can be used for other regions of musculoskeletal pain. The short version has been shown to be appropriate for clinical and research purposes, since it is nearly as accurate as the original, longer version [26].

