##### Drug consumption

Consumption of pharmaceutical drugs that can be related to the musculoskeletal condition for which the participant is treated (ATC codes M – musculoskeletal system and N – nervous system) will be estimated using data from the Swedish registry for drug use, regarding filled prescriptions. Data will be collected for a 3-month period before baseline and for the 12-month period after baseline. Self-reported drug consumption, both prescription and nonprescription drugs, will be collected via the questionnaire.

Other secondary outcome measures are loss of productivity and healthcare costs and incremental cost-effectiveness ratios [17].

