### Data collection

For the primary outcome sickness absence, data will be collected from the SSIA and self-reported short-term sickness absence will be collected weekly from the participants as described above.

For the secondary outcomes, an email is sent to the patient with a link to the questionnaire where the patient-reported data will be collected using the self-administrated instruments at inclusion (baseline), at one and 3 months after inclusion (short-term follow-up), and at six and 12 months after inclusion (long-term follow-up). Data on age, gender, location of birth, education, family, present employment or source of income, and symptom duration will be collected at inclusion. The patient drawing of the pain sites marked on an anatomical sketch of a human body is sent out separately by mail and returned in a pre-paid envelope. A reminder is sent by email once per week during 4 weeks, to promote participant retention and complete follow-ups. For the patient drawing, one reminder is sent out after 2–3 weeks by mail. If a patient wishes to withdraw from the study or further follow-ups, he or she is asked to approve the collection of registry data from SSIA and the Swedish registry for drug consumption.

Data on interventions received in both the PREVSAM and the TAU group will be collected from the participant’s electronic medical record, which also will be used for monitoring of intervention adherence/treatment fidelity. The interdisciplinary teams are instructed to report on solicited and spontaneously reported adverse events and other unintended effects of trial interventions or trial conduct. Any concomitant interventions provided for the same diagnosis will be collected via Region Västra Götaland’s healthcare utilisation database (VEGA).

Outcome data from the web-based questionnaire will be transferred to a database, where it will be checked for accuracy by the research assistant to promote data quality.

There will be no data monitoring committee since the study is independent from the sponsor and the intervention consists of a rehabilitation model that includes evidence-based treatment methods with little risk for unexpected adverse events.

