Group characteristics will be presented as mean and standard deviations, median and 25th and 75th percentile or the number and percentage. For the primary outcomes descriptive analyses for sickness absence for the two groups will be presented according to recommendations [31]. The sickness absence will be presented with number of individuals who had sickness absence during the follow-up period. Proportions of individuals with sickness absence per month will be presented. The number of sick days (gross and net) with sickness benefit during the follow-up periods will be presented with mean and median values. For participation in work life additional measures will be presented with descriptive statistics regarding time to sick-leave spell for musculoskeletal pain. Number of days before a sick leave spell > 14 days occurs and number and duration of sick-leave spells per individual will be presented for gross and net days. Outcomes will be analysed according to intention-to-treat. Multivariable logistic regression analysis will be used for the primary outcome sickness absence during the follow-up period [1], not being sickness absent (0) adjusted for confounders. Multivariable linear regression analyses, or possibly quantile regression, will be used to evaluate differences between groups for sick leave days, among those have at least one sick leave spell. All other measurements will be analysed by calculating raw differences between baseline and follow-up assessments. Parametric and non-parametric tests will be used depending on data level and distribution. Sub-group analyses can be performed in regard to characteristics of interest, such as diagnosis or sick-leave. The level of significance is set to *p* < 0.05. Relevant statistical programs will be used for the statistical analyses, for example the IBM SPSS, SAS, STATA.

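### Secondary outcomes are analysed as raw change from baseline, which costs precision that adjusting for the baseline value would keep, and which does not suit registry drug use or weekly text-message absence

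*Protocol article*

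**What the plan says.** The Statistical analyses section gives the two primary sickness-absence outcomes their own multivariable models. It then covers the rest in two sentences: "All other measurements will be analysed by calculating raw differences between baseline and follow-up assessments" and "Parametric and non-parametric tests will be used depending on data level and distribution". No covariate is named for these comparisons.

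The Data collection section confirms that baseline values will exist: "patient-reported data will be collected using the self-administrated instruments at inclusion (baseline), at one and 3 months after inclusion", and again at 6 and 12 months.

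Four other places bear on the point:

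- Drug consumption, on the registry data: "Data will be collected for a 3-month period before baseline and for the 12-month period after baseline".
- Primary outcome: short-term absence is reported weekly by text message after inclusion, and no pre-inclusion value is described. The Abstract lists this measure among the secondary outcomes.
- Patient-reported risk for sickness absence: the ÖMPSQ-SF outcome has its own definition, "proportion lowering their risk by scoring < 40 p at follow-up".
- Randomisation: envelopes are prepared in blocks of six, three per arm. "These are placed in a box at each participating centre".

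**The concern.** A raw difference subtracts the whole baseline value, so it fixes the baseline coefficient at 1. The best coefficient is usually smaller, and the gap adds noise to the comparison between arms. Research questions Q2 to Q4 (work ability, pain, self-efficacy, disability, quality of life, risk score, anxiety and depression, drug use) would then be answered with wider intervals than the same data allow.

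This is a method that the text states, not a detail left open. An analysis plan that used baseline adjustment would depart from the published sentence.

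The sentence is also worded to cover all remaining measurements, and for two of them a difference from baseline does not work. The registry drug windows differ in length, and weekly text-message absence has no described baseline.

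**Working it through.** **The plan's own figures.** The article gives no precision or power figure for any secondary outcome, so there is none to reproduce on this point. Its 132 per group belongs to the binary primary outcome. That figure reproduces to within two (134 with a continuity correction, two-sided) but does not bear on the change score. From the plan I use 200 randomised per group, α = 0.05 (taken as two-sided) and 80% power.

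**Assumed inputs.** The documents give neither the baseline-to-follow-up correlation r nor a centre intraclass correlation (ICC), so both are shown as ranges.

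**Step 1: equal variances.** In units of the follow-up variance, the between-arm contrast has variance proportional to

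- 2(1 − r) for the raw change,
- 1 for follow-up alone,
- 1 − r² for the follow-up value adjusted for baseline (ANCOVA).

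The ratio of ANCOVA to change is (1 − r²)/[2(1 − r)] = (1 + r)/2. Power of the change score where ANCOVA has 80% is Φ(2.80·√ratio − 1.96). The smallest difference detectable with 80% power at 200 per group is 2.80·√(2/200) = 0.280 follow-up SDs, times the square root of the relevant variance.

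| r | change | ANCOVA | ratio | power of change | detectable difference, change vs ANCOVA |
|---|---|---|---|---|---|
| 0.3 | 1.40 | 0.91 | 0.65 | 62% | 0.33 vs 0.27 |
| 0.5 | 1.00 | 0.75 | 0.75 | 68% | 0.28 vs 0.24 |
| 0.7 | 0.60 | 0.51 | 0.85 | 73% | 0.22 vs 0.20 |
| 0.8 | 0.40 | 0.36 | 0.90 | 76% | 0.18 vs 0.17 |

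Below r = 0.5, 2(1 − r) exceeds 1, so the raw change is less precise than not using the baseline at all.

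**Step 2: unequal variances.** Let k be baseline SD divided by follow-up SD. The change-score variance is 1 + k² − 2rk. Subtracting the ANCOVA variance 1 − r² leaves (k − r)², which cannot be negative. So in large samples the change score is never the more precise, and the two are equal only when k = r. At an assumed k = 0.7, as truncation at entry might produce:

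- r = 0.3: 0.91/1.07 = 0.85, a loss of 15%
- r = 0.5: 0.75/0.79 = 0.95, a loss of 5%
- r = 0.7: 0.51/0.51 = 1.00, no loss

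**Step 3: centre.** With 1:1 blocks held at each centre, allocation is in effect stratified by centre. Leaving centre out makes the standard error too large by a factor 1/√(1 − ICC): 1.005 at ICC 0.01 and 1.054 at ICC 0.10. The true two-sided error rate is then 0.049 to 0.039, and power is 79.7% to 76.9% where the analysis with centre has 80%.

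**Step 4: drug windows.** A patient who uses a constant amount m per month has 3m before baseline and 12m after. The raw difference of totals is 12m − 3m = 9m, an apparent rise of three times the baseline total with no change in use.

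**The case against.** The strongest reply is that the loss may be small. The figures in Step 1 rest on an assumed r and on equal variances. Entry requires an ÖMPSQ-SF score of at least 40, which tends to narrow the baseline spread of that score, and at k = 0.7 the loss falls to between 0% and 15%. The formula also does not describe the 4-point pain frequency item, the banded pain duration, or outcomes analysed by rank tests. All of this stands, so no single percentage can be given for the secondary outcomes as a group.

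It can also be said that the sentence refers to the repeated questionnaire instruments and was never meant for registry totals or text messages. The Outcomes section places text-message absence under the primary outcome, and nothing says that a 3-month total will be subtracted from a 12-month one. That reading is reasonable, but the sentence claims all other measurements and gives no separate rule for these two.

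A reader might infer several stronger points that the document does not support:

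- **That baseline is ignored.** It is not. The change score uses it, with a fixed coefficient.
- **That no model includes centre.** No centre term is named, but the primary logistic model is "adjusted for confounders" and the sick-days model is multivariable. Neither covariate list is printed, centre may be in either, and such lists commonly sit in an analysis plan.
- **That covariates will be picked after seeing the data.** Nothing says so.
- **That regression to the mean from the entry cut-off worsens imbalance.** The cut-off applies to both arms, so the shift is the same in expectation and cancels in the contrast.
- **That the proportion scoring below 40 should be made descriptive.** It is a defined outcome of its own, and demoting it would be a preference.

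**Conclusion.** The point holds for the secondary outcomes. The stated raw-difference analysis is, for continuous measures in large samples, never more precise and usually less precise than adjusting the follow-up value for baseline. With equal variances the loss is equivalent to 35% of the sample at r = 0.3, 25% at r = 0.5 and 15% at r = 0.7. It is less if baseline variance is restricted. The values of r and k are assumptions, while the direction is not.

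It is a loss of efficiency and not a bias, and it leaves the primary comparison untouched. The gain from a centre term is minor: standard errors about 0.5% to 5% too large without it at an assumed ICC of 0.01 to 0.10, in the conservative direction. It also rests on stratification that the envelope boxes imply but the text does not state. Separately, and without any assumed r, a literal difference of registry drug totals would mislead, and a change score for weekly text-message absence has no baseline to subtract.

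**What to change.** Replace the raw-difference sentence with outcome-specific wording:

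1. **Continuous questionnaire outcomes:** model the follow-up value on group and baseline value, either by ANCOVA at each time point or by a mixed model over 1, 3, 6 and 12 months. Include centre as a random effect or stratum.
2. **Registry drug use:** analyse the follow-up rate per unit time, with the 3-month pre-baseline rate as covariate.
3. **Weekly text-message absence:** compare reported days by arm, without a change score.
4. **Proportion scoring below 40 on the ÖMPSQ-SF:** leave as defined.

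The cost is analysis wording only. The questionnaire baselines and the pre-baseline drug data are already to be collected, and centre is known from where the patient was randomised. The wording should be settled before the interim analysis, because the Statistical analyses section allows the short-term outcomes to be analysed at that point.

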### Ethical considerations and data management

Even though the intervention does not include any new technology per se, but rather a more comprehensive, yet focused, rehabilitation model, several ethical issues need to be considered. Screening for a condition can sometimes be controversial. There might be a risk that we find too many cases and “overtreat” these people. However, if the study does not find any benefits of the new model, we will have a clear indication that there is no need to introduce this more comprehensive model at an early stage.

There is also a possibility that people are hesitant about healthcare professionals approaching and collaborating with their employer. However, clinical experience has shown that people often perceive that the healthcare system can be a legitimate channel to reach the employer to explain the needs, and also to stress the responsibilities of each part.

Eligible participants who meet the inclusion criteria and preliminary agree to participate, will receive oral and written information, including the written consent form, by a healthcare professional at the study centre, before or at their first visit to the clinic. The information includes that participation is voluntary and that they may withdraw participation at any time, without any consequences for their continued treatment or rehabilitation. If the patient accepts participation, he/she returns the signed informed consent to the study centre and these are collected by the project coordinator. The informed consent can also be sent back by mail to the project coordinator. In the informed consent the participants also consent to collection of registry data.

The study will involve collection and management of personal demographic and outcome data, which will be treated with high respect for the persons’ integrity. All collected data will be coded and a code list will be created, giving the possibility to go back and double check raw data. Data and code list will be stored separately and will only be accessible by authorised members of the research team, as will the final trial dataset. Data will be managed according to Swedish law and in compliance with Region Västra Götaland’s data management guidelines. This includes registry with the Data Protection Officer of Region Västra Götaland and storage in a locked and fireproof safe and on access-controlled servers with high levels of security.

A data management plan (DMP) has been developed, which provides details on how data are collected, managed during and after the project, documented, stored and archived, and made available, including, where, when, how and to whom. The DMP can be provided on reasonable request from the corresponding author. Routines for data storage from Region Västra Götaland will be followed and meta data standards will be used to describe the data material. A data management team will manage and monitor data accuracy and quality, and comprises the principal investigator, a postdoc or senior researcher, a project coordinator, and a research assistant.

### Timeline

A timeline and schedule of enrolment, interventions, and assessment is presented in Fig. 2.

**Fig. 2 Fig2:**
[figure not shown]
Schedule of enrolment, interventions, and assessments. TAU, Treatment as usual

### Process evaluation

In parallel to the intervention, a process evaluation is planned, in which implementation and process outcomes will be monitored, documented, and assessed [49]. All interventions delivered will be documented and closely monitored to enable evaluation and further development of the rehabilitation model, in which issues such as detailed intervention components, treatment/model fidelity, and training will be addressed. The process evaluation will facilitate future implementation and scale-up of the intervention, should it be found effective in this study.

### Dissemination and implementation of study findings

This study protocol will be published in an open access journal to allow free public access. The study findings will be disseminated and made publicly available in peer-reviewed publications and conference presentations. The results will also be disseminated, through regular dissemination and communication channels, within and outside health care and university contexts. The Swedish research Council for Health, Working Life and Welfare that sponsors the study usually organises conferences to disseminate results from studies they sponsor. Since the planned study focuses on collaboration both within health care and with employers and the SSIA, communication strategies targeting these stakeholders will be developed.

## Discussion

This randomised controlled trial will evaluate the effects of a new rehabilitation model that comprises interdisciplinary, person-centred interventions for individuals with musculoskeletal pain who are at risk for persistent pain, physical disability and sick leave. Effects on sickness absence and various patient-reported health outcomes will be measured. The study is expected to show whether a rehabilitation model of this nature can be a feasible method in a primary care context to prevent or reduce sickness absence due to musculoskeletal pain.

The pragmatic nature of the PREVSAM model and its closeness to current clinical practice provide a clinical advantage and will make the intervention easy to implement throughout the county and beyond. The study will provide new knowledge on if identifying patients with musculoskeletal pain at risk for sickness absence and development of persistent pain, and providing this structured, person-centred, interdisciplinary rehabilitation is more effective than treatment as usual. The long-term implications of the study are to optimise rehabilitation for this large patient group, which may through secondary prevention of pain help reducing sick leave and improving return to work rates and participation in society, as well as reduce costs for both healthcare and society.

Year 2008, multimodal rehabilitation (MMR) programmes were initiated with governmental support in the form of “Rehabilitation guarantee”, but neither evaluations in Region Västra Götaland nor other regional or national evaluations found any significant reductions in sickness absence [50–52]. The PREVSAM model is designed to be feasible to perform within the existing “Care choice rehabilitation of primary care” context in the Region Västra Götaland, if showed to be effective, successful implementation will probably require adjustments in the reimbursement system; e.g. reimbursement will be required also for psychological interventions within rehabilitation team meetings, as well as meetings and activities at the workplace. There has been an ongoing debate for at least 25 years whether health care should be performing actions at or in collaboration with the workplace; however, interventions including healthcare provision in combination with service coordination and work accommodation have been recommended to improve work functioning and reduce costs [21]. Although there is general consensus that health care has the competence of doing so, the discussion is still about reimbursements. A recent study showed that workplace dialogue in addition to physiotherapy improved work ability significantly in patients with acute/subacute neck and/or back pain [29], and that the combination of workplace dialogue and physiotherapy was cost-effective from both a societal and a healthcare perspective [53]. It has also been shown that occupational therapy interventions increase return to work rates [54] and, that cognitive behavioural therapies showed positive results on return to work and sick leave for people with chronic illnesses [55]. In this study the physiotherapist, the occupational therapist, and the psychotherapist constitute the core interdisciplinary team.

The costs for the PREVSAM rehabilitation model described in this protocol, if implemented on a large scale, are expected to be modest and the intervention is likely to yield similar cost-effectiveness when treatment costs are weighed with the indirect costs of sickness absence.

Because the return-to-work process for individuals who are sick-listed is costly for both individuals, health care and society, it is of great importance to find ways of preventing sickness absence and of keeping acute or subacute musculoskeletal pain from becoming persistent. Our study is expected to provide new knowledge regarding the effectiveness of a rehabilitation model that may be one such way, and its feasibility in a primary care context.

